### Bariatric surgery

Only subjects that will be submitted to Roux-en-Y gastric bypass are included in this trial. The surgical procedure is performed by the same surgeon according to Hospital CUF Tejo protocol that follows the 2019 bariatric surgery guidelines [3]. Likewise, all the pre and post-surgical appointments, interventions and recommendations will follow Hospital CUF Tejo protocol [17].

### Intervention, compliance, and adverse effects

Participants enrolled in the trial are randomly assigned to receive either probiotic or placebo. The probiotic or placebo is orally taken, twice a day, with one glass of water, approximately 5 min before both breakfast and lunch, for 90 days, between 3 and 6 months after bariatric surgery. Two capsules of the probiotic contain 5 × 10^7^ CFU of *Hafnia alvei* HA4597™, 5 mg of zinc and 20 μg of chromium. The capsules are gastro-resistant which allows the ingredients to resist stomach acidity. A placebo is used as a comparator to determine if the probiotic effect is directly related with the strain (i.e. *Hafnia alvei*). The placebo product is indistinguishable in colour, smell, and taste from the active formulation, and has the same composition but without the live bacteria.

To improve compliance, participants will receive a message every 2 weeks and a call approximately 45 days after starting the intervention to reinforce the intake of the capsules and to register any missing intake on the calendar provided by the research team.

#### Safety monitoring and compliance

Participants are asked to remark on a daily basis in a paper diary any adverse effects during the intervention. Likewise, the research team also monitors all participants throughout the study (through bi-weekly messages and a call) for any adverse events, in particular gastrointestinal symptoms and possible allergies. In case of serious adverse effects, a thorough follow-up will be conducted to investigate the incident and participants will be advised to stop taking the capsules immediately.

To evaluate compliance, participants register the daily intake of the capsules during the 90 days of intervention and are asked to return all the used and unused bottles with the remaining capsules (if any). It is not specified any concomitant care to be permitted or prohibited.

## Outcomes

An overview of the primary and secondary outcomes, descriptive data and timing of assessment is displayed in Table 1.

**Table 1 Tab1:**
[figure not shown]
Assessment schedule

*FFQ* Food frequency questionnaire, *FRs* Food records, *HbA1c* Glycated haemoglobin, *HOMA-IR* Homeostatic model assessment of insulin resistance, *HOMA-β* Homeostasis model assessment of β-cell function, *HOMA-S* Homeostasis model assessment of insulin sensitivity, *HDL* High-density lipoprotein cholesterol, *LDL* Low-density lipoprotein cholesterol, *VLDL* Very-low-density lipoprotein cholesterol, *ALT* Alanine aminotransferase, *AST* Aspartate aminotransferase, *GGT* Gamma-glutamyl transferase, *GLP-1* Glucagon-like peptide-1, *GIP* Gastric inhibitory polypeptide, *TMAO* Trimethylamine N-oxide, *IPA* Indole-3- propionic acid, *ImP* Imidazole propionate, *ClpB* Caseinolytic peptidase B protein homolog, *TGF* Transforming growth factor, *MCP* Monocyte chemoattractant protein, *IFN* Interferon, *IL* Interleukin

### Primary outcomes

The primary outcomes are the differences in the number of subjects that will lose at least 50% of excess weight, as well as the number of subjects that will have glycated haemoglobin levels lower than 5.7%, between the probiotic and placebo groups, 1 year after the surgery. The rationale behind the primary outcomes is based on previous studies that have described the effect of *Hafnia alvei* HA4597™. In the preclinical study conducted by Legrand et al. [14], the effect of *Hafnia alvei* HA4597™ supplementation was assessed in two models of obesity, in leptin deficiency *ob/ob* mice and high-fat diet (HFD)-fed obese and overweight mice. Results showed that in both models’ body weight gain was significantly lower by the end of the study (50.1% *ob/ob* and 38.1% HFD), as well as fat gain (38.3% *ob/ob* and 51.9% HFD) [14]. In addition, loss of lean mass was 126.8% lower and food intake reduced 20.8% in the *ob/ob* mice [14]. A second trial was conducted by Lucas et al. [11] using a mice model of obesity characterized by a combination of a HFD-fed obese and a genetic *ob/ob* mice which closely represents the hyperphagia and diet-induced obesity in humans (compulsive eating behaviour combined with hypercaloric diet and functional leptin resistance). The authors observed that *Hafnia alvei* HA4597™ supplementation resulted in 58.1% lower body weight gain, decreased food intake and fat mass gain, and increased lean mass preservation, resulting in an improved lean/fat mass ratio [11]. Moreover, *Hafnia alvei* HA4597™ treatment also improved metabolic outcomes, including glycemia. Basal glucose levels decreased by 1.5-fold compared to standard diet HFD-fed controls [11]. Afterwards, the efficacy of *Hafnia alvei* HA4597™ supplementation was tested in humans [15]. A randomized, placebo-controlled, double-blind trial evaluated the effect of this probiotic (5 × 10^7^ CFU of *Hafnia alvei* HA4597™) on 236 overweight men and women that were following a low-calorie diet [15]. After 12 weeks, significantly more subjects (+ 51%) lost at least 4% of their initial weight comparing to placebo [15]. Furthermore, compared to placebo, subjects in the treatment group had a significant reduction in hip circumference and glycemia, and increased feeling of fullness, which was assessed by a visual analogue scale [15].

Thus, preclinical and clinical results with *Hafnia alvei* HA4597™ are very promising in regard to weight loss and glycaemic levels reduction. Therefore, these outcomes are crucial to validate the effect of *Hafnia alvei* HA4597™ supplementation in an obese population and assess its contribution to the success of bariatric surgery.

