**Methods:**

This is a protocol of a triple-blinded, blocked-randomized, parallel-group, placebo-controlled clinical trial designed to determine the effect of *Hafnia alvei* HA4597™ supplementation on weight loss and glycaemic control 1 year after bariatric surgery. Patients of Hospital CUF Tejo, Lisbon, that undergo Roux-en-Y gastric bypass are invited to participate in this study. Men and women between 18 and 65 years old, with a BMI ≥ 35 kg/m^2^ and at least one severe obesity-related comorbidity, or with a BMI ≥ 40 kg/m^2^, and who are willing to take 2 capsules of *Hafnia alvei* HA4597™ probiotic supplements (equivalent to 5 × 10^7^ CFU) *vs*. placebo per day for 90 days are included in this study. Assessments are carried out at baseline, 3, 6, 9, and 12 months after the surgery. Loss of weight in excess and glycated haemoglobin are considered primary outcomes. In addition, changes in other metabolic and inflammatory outcomes, gut microbiota composition and metabolites, as well as gastrointestinal quality of life are also being assessed during the trial.

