## Background

Management of obesity stands primarily on achieving an adequate weight loss to reduce its impact on quality of life, morbidity and mortality risk [1, 2]. For patients who are unable to achieve clinically relevant weight loss through therapeutic lifestyle or pharmacological measures, bariatric surgery is considered the most effective intervention for weight loss, prevention of weight regain, and improvement, as well as remission, of many obesity-related comorbidities [3]. Nevertheless, over 20% of all patients do not lose enough weight 1 year after bariatric surgery (< 50% excess body weight) and there is also risk of weight regain after the surgery [4]. Non-adherence to post-surgery dietary recommendations has been reported in 23% of patients, contributing significantly to weight regain [5]. Therefore, identification of new strategies to sustain appetite control to maintain weight loss and metabolic recovery after the surgery is warranted.

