## Sample size

Sample size calculations have considered the outcomes: percentage of excess weight loss and fasting blood glucose levels. Based on previous studies with a population similar to this study, the assumed standard deviation was 10.70 for percentage of excess weight loss [37] and 14.00 mg/dL for fasting blood glucose [38]. To detect a difference of 10.48% [39] in excess weight loss and 11.30 mg/dL [40] in fasting glucose between the intervention and placebo group after 1 year of follow-up, it was determined that 44 participants are required to allow for an 80% power and 95% confidence level. Compensating for possible attrition, 30% additional samples will be recruited, representing a total of 58 participants (29 in each arm — probiotic group and placebo group). Considering that Hospital CUF Tejo receives around 80 patients each year to be submitted to bariatric surgery, of these around 70% are Roux-en-Y gastric bypass, assuming that 29% of the subjects will not be eligible to participate [39], it is anticipated that it will take approximately 18 months to recruit this sample size.

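### The stated 80% power applies to neither declared primary outcome: the trial is sized on mean excess weight loss and fasting glucose but judged on two responder counts

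*Protocol article*

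**What the plan says.** The Primary outcomes section is the only place that gives a threshold, a time point and a contrast. It reads "The primary outcomes are the differences in the number of subjects that will lose at least 50% of excess weight", and adds "the number of subjects that will have glycated haemoglobin levels lower than 5.7"%, compared between probiotic and placebo 1 year after surgery. Both are binary.

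The Sample size section works with other variables: "Sample size calculations have considered the outcomes: percentage of excess weight loss and fasting blood glucose levels". Its inputs are means and standard deviations: "the assumed standard deviation was 10.70 for percentage of excess weight loss", "14.00 mg/dL for fasting blood glucose", and "To detect a difference of 10.48" percentage points of %EWL and 11.30 mg/dL of glucose. From these it derives 44 participants for 80% power at 95% confidence, raised to 58 for attrition.

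Study objectives and Secondary outcomes both place fasting glucose among the secondary measures. HbA1c does not appear in the sample size text, and no responder rate is given for either arm on either primary.

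The Abstract names the primaries without cut-offs: "Loss of weight in excess and glycated haemoglobin are considered primary outcomes". The aims in Study objectives likewise refer to the percentage of excess weight loss and to HbA1c.

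**The concern.** A power statement tells the reader how likely the trial is to detect the planned effect on the outcome that decides it. Here it describes different variables. The weight variable is the same measurement but has been cut at 50%, and the Background says that "over 20% of all patients do not lose enough weight 1 year after bariatric surgery", where insufficient loss means under 50% of excess weight. If the placebo arm behaves similarly, roughly four in five already succeed, there is little room above them, and the cut discards much of the information in the measurement. For glycaemia the variable itself changes, from HbA1c to fasting glucose.

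At stake is how a non-significant primary result is read. It would be taken as the outcome of an 80%-powered trial when the chance of detecting the assumed benefit could be much lower, and for HbA1c is unknown.

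**Working it through.** **1. The plan's own figure.** Inputs from Sample size, with two-sided 0.05 assumed because sidedness is not stated. Per arm, n = 2 × (1.960 + 0.842)² × (SD/difference)².

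- %EWL: 15.70 × (10.70/10.48)² = 16.4, so 17 per arm (18 by the t-distribution), 34 to 36 in total.
- Fasting glucose: 15.70 × (14.00/11.30)² = 24.1, so 25 per arm (26 by the t-distribution), 50 to 52 in total.

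The stated 44 matches neither. At 22 per arm the t-based power is about 89% for mean %EWL and 74% for fasting glucose. The 58 is 44 × 1.3 = 57.2, rounded up, which is 29 per arm.

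**2. The same effect on the declared weight outcome.** Assumptions: %EWL is normal with SD 10.70 in both arms, the probiotic shifts it by 10.48, and the placebo success rate is 80%. The last is taken from the Background figure of just over 20% failing, which describes bariatric patients in general.

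- Placebo mean: 50 + 0.842 × 10.70 = 59.0.
- Probiotic mean: 59.0 + 10.48 = 69.5.
- Probiotic success rate: Φ((69.5 − 50)/10.70) = Φ(1.82) = 96.6%.

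The comparison is therefore 80% against 96.6%.

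**3. Power for that comparison.** Statistical analysis names the chi-square test for categorical variables. All possible tables were enumerated with the uncorrected test at 0.05:

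| Placebo rate | Implied probiotic rate | Power, 22 per arm | Power, 29 per arm (no losses) |
|---|---|---|---|
| 50% | 83.6% | 67.1% | 79.1% |
| 60% | 89.1% | 62.9% | 74.5% |
| 70% | 93.4% | 55.2% | 66.9% |
| 75% | 95.1% | 49.7% | 62.4% |
| 80% | 96.6% | 41.5% | 55.6% |
| 85% | 97.8% | 29.2% | 43.9% |
| 90% | 98.8% | 13.6% | 24.9% |

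At the 80% rate and 22 per arm, the average number of failures per arm is 22 × (0.20 + 0.034)/2 = 2.6. Cells that small would often lead an analyst to Fisher's exact test, whose power is 26%. By the usual normal-approximation formula, 80% power at this rate needs about 58 evaluable per arm, as many in each arm as the trial plans to recruit altogether.

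**4. HbA1c below 5.7%.** No rate, difference or SD is given, so power cannot be computed. Purely as illustration, at 22 per arm an assumed 50% against 70% has about 27% power, and 50% against 75% about 40% (normal approximation).

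**The case against.** The sponsor can fairly say four things.

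First, the responder power rests on a borrowed rate. The Background figure covers bariatric patients generally, whereas this trial takes only Roux-en-Y bypass. It also says over 20% fail, so on that anchor the placebo rate is at most about 80%. The 85% and 90% rows run against it, and the rates below 80% are kinder to the design. This stands: 42% is conditional and should not be presented as the true power.

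Second, 22 per arm is the planned low end. Statistical analysis keeps non-compliers and those lost to follow-up in the intention-to-treat analysis and draws on medical records, so numbers nearer 29 per arm are possible. A reader might infer that a null result is to be expected even if the effect is real. The documents do not support that: at 29 per arm and an 80% rate, success is slightly more likely than not.

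Third, a reader might count three rival versions of the primary outcome. The Abstract and the aims name variables without calling them continuous, means or changes, and Sample size never calls fasting glucose primary. The firm conflict is the single one between Primary outcomes and Sample size.

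Fourth, the 50% threshold has a rationale in the article, and a responder primary is legitimate. That also stands, but such a primary still needs a power statement of its own.

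None of this supplies a calculation for either declared primary. Nor is the gap a detail left to a fuller document, since the article states both the outcomes and the sizing basis.

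**Conclusion.** The concern holds. The 80% power does not apply to either declared primary outcome. For at least 50% EWL, power is about 42% at 22 per arm and 56% at 29, given normality, the protocol's own shift and SD, and an assumed 80% placebo rate. The exact values depend on that rate, but across 50% to 90% none reaches 80% at either size. For HbA1c below 5.7% nothing can be calculated.

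A reader might also conclude that the 80% is at least right for mean %EWL. It is not: at the stated inputs, 22 per arm gives more than 80% for mean %EWL and less than 80% for fasting glucose.

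**What to change.** Before unblinding, take one of two routes.

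- Make the between-arm difference in mean %EWL at 12 months the primary weight outcome, which fits both the stated aim and the sizing basis, and keep at least 50% EWL as a secondary responder outcome.
- Or keep the responder primary and replace the 80% claim with its own power: about 42% at 22 per arm and 56% at 29 for an 80% placebo rate, with the assumptions and the range shown.

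Under either route, do not write that 80% applies to mean %EWL. Give about 89% for mean %EWL and 74% for fasting glucose at 22 per arm. For HbA1c, state that no power claim is made unless a planning difference and SD, or responder rates, are supplied. Switching to continuous HbA1c would not cure this, because no planning figure exists for that form either.

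The cost is a protocol and registry amendment. The article reports recruitment as ongoing, so a change of primary would come mid-trial and its timing and blinded status should be documented. The second route also means publishing a less favourable power. Neither needs extra patients or measurements, since weight is already recorded at every visit.

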#### Recruitment and eligibility criteria

Men and women between 18 and 65 years, with a BMI ≥ 35 kg/m^2^ and at least one severe obesity-related complication, or with BMI ≥ 40 kg/m^2^, that will undergo Roux-en-Y gastric bypass for the first time are informed on the trial and invited to participate. Volunteers are recruited after their first surgery appointment and are given at least 1 week to consider their possible participation. Afterwards, if the volunteer decides to participate and agrees to take a probiotic/placebo supplement twice a day for 90 days, the volunteer is asked to give a written informed consent. Subjects are excluded from the study if one or more of the following conditions are met:Intake of antibiotics and/or probiotics in the previous 12 weeksWeight change > 5% in the previous 12 weeksUnder corticotherapy or under other anti-inflammatory drugsDiagnosis of gastrointestinal disease or other significant illnessPregnancy or breastfeeding

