#### Randomization, allocation, and blinding

Eligible participants are randomized using block randomization in a 1:1 ratio to either the probiotic or the placebo group. Blocked randomization is stratified according to HbA1c levels obtained at first visit (baseline), following American Diabetes Association guidelines for pre-diabetes and diabetes diagnosis (normal: < 5.7%; pre-diabetes: 5.7–6.4%; diabetes: ≥ 6.5%) [16]. The randomization is performed using the National Cancer Institute clinical trial randomization tool (https://ctrandomization.cancer.gov/). A minimisation method is used on the allocation process to ensure the required balance across the intervention and control groups. Results are sent to an independent researcher responsible for allocation that is not involved in the recruitment nor in the delivery of the intervention. The allocation is performed right before the beginning of the intervention of each group of randomized participants (in blocks), sending the results to a local researcher in a pre-printed Excel worksheet (Microsoft, Redmond, WA, USA). Randomization and allocation of participants are carried out by different researchers.

The study products are packaged and blinded by an outsourced pharmacy. The package appearance of both products is identical; thus, participants and care providers will be blinded to the intervention. All researchers involved in the trial are also blinded to the intervention allocation until the trial is completed. At the end of the study, researchers performing the statistical analysis will divide the participants into the coded groups and will be unaware regarding the intervention allocation. A member of the research group that is not involved in the study nor participates in the investigation meetings is responsible to keep the sealed envelopes with the allocation of each code in a locked drawer. After performing the analyses, the sealed envelope will be opened by the coordinating and principal investigators.

Unblinding will be needed in case of medical event emergencies or serious medical conditions that may occur during the trial whereby the physician needs to know which treatment they have been receiving. However, given the nature of the intervention and placebo, it is unlikely to occur.

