### Anthropometry and body composition

Height is measured to the nearest 0.1 cm with a wall stadiometer (SECA®, Hamburg, Germany), following the Directorate-General for Health protocol [24]. Participants remove their clothes, socks, and any metal objects prior to measurement of body weight and body composition (including percentage of fat mass, fat mass, fat-free mass and skeletal muscle mass) by tetrapolar bioimpedance (Inbody®, model 770, Seoul, Korea). Body mass index is also obtained by the device report and percentage of excess weight loss is calculated as: $$\frac{\mathrm{baseline\,weight}\left(\mathrm{kg}\right)-\mathrm{follow\,}-\mathrm{\,up\,weight}\,(kg)}{\mathrm{baseline\,weight}\left(\mathrm{kg}\right)-\mathrm{ideal\,weight\,for\,BMI\,}25\mathrm{\,kg}/\mathrm m^2}\times100$$ [25]. Weight and body composition is measured at all visits.

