## Recruitment status

The patient recruitment is still ongoing, it has started in March 2022 and is expected to be completed by June 2023. To date, 30 subjects have been recruited and 14 were considered eligible and agreed to participate in this trial. The mean age of the eligible participants is 46 years and 50% of subjects are female. At baseline, participants had an average weight of 129.7 kg and an average height of 1.70 m, which corresponds to an average body mass index of 44.9 kg/m^2^ (class III obesity). Moreover, mean glycated haemoglobin was 6.3%, which falls in the reference interval for pre-diabetes.

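### The excess-weight-loss outcome depends strongly on entry BMI, yet baseline BMI is not prespecified in the between-arm comparison, which costs precision

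*Protocol article*

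**What the plan says.** Under Primary outcomes, the weight outcome is the between-arm difference in "the number of subjects that will lose at least 50% of excess weight" at one year. The primary aims and the sample size section work with %EWL as a continuous measure. Under Anthropometry and body composition, "percentage of excess weight loss is calculated as" weight lost divided by baseline weight minus the weight at BMI 25, times 100.

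Patients enter "with a BMI ≥ 35 kg/m^2^ and at least one severe obesity-related complication", or at BMI 40 and above without one. No upper limit is given. Recruitment status reports a mean weight of 129.7 kg and height of 1.70 m in the first 14 participants, "which corresponds to an average body mass index of 44.9"; no SD is given.

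On allocation: "Blocked randomization is stratified according to HbA1c levels obtained at first visit (baseline"), in three HbA1c bands. The same section adds: "A minimisation method is used on the allocation process to ensure the required balance across the intervention and control groups". The minimisation factors are not named.

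Statistical analysis names a chi-square test for categorical outcomes and a t-test or a rank test for continuous ones, none with a covariate. (The t-test and rank test are given in paired form, which is a separate matter.) The section also says, in general terms, that possible confounders will be looked at in each model. It plans a regression to find baseline predictors of excess weight loss. The subgroup factors it lists are age, gender and type 2 diabetes, followed by an open-ended et cetera.

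**The concern.** The denominator grows with entry BMI faster than body weight does, so the same proportional loss scores very differently. A patient who loses 20% of body weight has 70% EWL at BMI 35 (a responder) and 40% EWL at BMI 50 (a non-responder). Entry BMI is therefore a built-in source of variation in the outcome, known before randomisation and already recorded. If the comparison leaves it out, that variation stays in the error term. In a trial of 58, a chance BMI difference between the arms also moves the estimate. At stake are the precision of a primary comparison and the ability to say, when the arms differ in BMI, how much of the result that explains.

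**Working it through.** **Inputs from the protocol.** The %EWL formula; entry BMI of 35 or more; mean BMI 44.9 (reproduced: 129.7 / 1.70² = 44.9); 29 per arm; planned %EWL difference 10.48 and SD 10.70.

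**Step 1: the threshold.** Loss needed for 50% EWL, as a percentage of body weight, is 50 × (BMI − 25) / BMI.

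| BMI | Calculation | Loss needed | kg at 1.70 m |
|---|---|---|---|
| 35 | 50 × 10/35 | 14.3% | 14.5 |
| 40 | 50 × 15/40 | 18.75% | 21.7 |
| 44.9 | 50 × 19.9/44.9 | 22.2% | 28.8 |
| 50 | 50 × 25/50 | 25.0% | 36.1 |

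From BMI 35 to BMI 50 the requirement rises by a factor of 25.0/14.3 = 1.75. This step needs no assumption.

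**Step 2: does it inflate false positives?** Null trials were simulated with BMI mean 44.9, SD 5 to 6; total weight loss mean 25 to 30%, SD 6 to 8, unrelated to BMI; 22 or 29 per arm; 20,000 trials per setting. The unadjusted chi-square test rejected in 4.4 to 5.8% of trials. A BMI gap of 3 units or more occurred in 2 to 9% of trials. When it did, the responder difference shifted by about 6 to 12 points, and the rejection rate in those trials was about 8 to 13%.

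**Step 3: how much variation is due to BMI?** Assumptions: BMI mean 44.9, SD 4 to 6, with only eligible values (35 or more) drawn; total weight loss mean 27 to 30%, SD 6 to 8, unrelated to BMI.
- Share of %EWL variance explained linearly by BMI: about 15 to 35% (one corner of the grid gives 13%).
- Share of responder variance explained: about 4 to 10% (one corner gives 12%).
- If adjustment removes a share R² of the variance, the unadjusted analysis needs 1/(1 − R²) times as many patients for the same precision. For %EWL this is 1/0.85 = 1.2 to 1/0.65 = 1.5. For the responder outcome it is at most about 1/0.90 = 1.1.

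**Step 4: effect of a one-standard-error imbalance.** The SE of the BMI difference is SD × √(2/29). Drawing eligible values only reduces the SDs of 4 to 6 to about 3.9 to 5.4, so the SE is about 1.0 to 1.4 BMI units. Multiplied by the regression slope on BMI, this moves mean %EWL by 1.9 to 2.8 points (18 to 27% of the planned 10.48) and the responder rate by about 2 to 4 points. For scale, at a 79% responder rate the sampling SE of the responder difference is √(2 × 0.79 × 0.21 / 29) = 10.7 points.

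**Step 5: consistency with the plan's SD.** These assumptions give %EWL an SD of about 16 to 22, against the planned 10.70. If every patient lost exactly 29%, a BMI SD of 4 to 6 alone would give an SD of about 8 to 11. The assumed spreads and the planned SD therefore cannot all be right, and the sizes in Steps 3 and 4 are illustrative.

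**The case against.** A reader might infer that chance BMI imbalance would pass for a treatment effect. The protocol does not support that. In a randomised comparison such imbalance is part of the error that the test allows for, and Step 2 shows the rejection rate staying near 5%. What remains is efficiency, and the estimate in the minority of trials with a large gap.

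A reader might also infer that the 50% rule mainly sorts patients by entry BMI. It does not. With total weight loss of mean 29% and SD 8, and BMI SD 6, BMI explains about 7% of responder variance and actual proportional loss about 44%. For the responder count, a one-SE shift of 2 to 4 points is small beside an SE of about 10.7. The larger gain is for continuous %EWL.

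Nor can it be said that weight is expressed only as %EWL. The assessment schedule (Table 1) is not shown, and weight and body composition are measured at every visit. The 50% benchmark has its own clinical rationale in the Background, so preferring percent total weight loss is a reporting choice.

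The best remaining defence is that BMI is unspecified rather than excluded: the minimisation factors are unnamed, confounders are to be evaluated, and covariates are often left to an analysis plan. The first two points are true, but neither puts BMI into the between-arm comparison. The article does fix the tests, and those are unadjusted. The predictor regression answers a different question. Choosing confounders after seeing the data is also weaker than naming one whose influence follows from the outcome's own formula.

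**Conclusion.** The point holds as one of precision and prespecification, not validity. That the threshold depends on BMI is certain from the protocol's formula. That BMI is absent from the named stratification factor and the named tests is plain from the text. The size is less certain because it rests on an assumed BMI spread, an assumed weight-loss distribution and independence between the two, none of which the protocol gives; the mean of 44.9 comes from only 14 participants. Within those assumptions, the loss is moderate for %EWL (equivalent to about 1.2 to 1.5 times the sample) and small for the responder count. The change is worth making because it costs almost nothing, but the trial's conclusions are not invalid without it.

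**What to change.** Before unblinding, prespecify baseline BMI in both forms of the weight outcome at 12 months:

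- **%EWL:** ANCOVA with treatment, baseline BMI (continuous) and the HbA1c stratum, reporting the adjusted mean difference with its 95% interval.
- **At least 50% EWL:** a model that includes baseline BMI, for example logistic regression with a standardised risk difference. Keep it small: if about 20% fail the benchmark, 58 patients give only about 0.20 × 58 = 12 non-responders. State a fallback, such as penalised estimation, for sparse data.

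State the minimisation factors, and whether BMI is one of them. Keep the 50% benchmark, and show the unadjusted responder counts beside the adjusted result. Percent total weight loss may be added as an optional supportive measure.

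The cost is a few sentences. Weight, height and BMI are already collected, and allocation and sample size are untouched. The drawback is a slightly more complex responder analysis in a small trial.
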